#### Statistical analysis of the secondary endpoints

For entomological outcomes, mosquito species composition will be reported as the total abundance and species-specific proportions of mosquitoes per sample per household per night. The outcomes will be compared across treatment arms. To address potential confounding factors and account for non-independence of data within clusters, logistic regression models will be employed, as described for the primary endpoint. Mosquito density will be reported as the total abundance of mosquitoes collected stratified by species. Additionally, for female *Anopheline* mosquitoes, the abundances will be broken down by blood fed/unfed, half gravid and fully gravid status. The outcomes will be compared across treatment arms. To address potential confounding factors and account for non-independence of data within clusters, a regression model will be employed with a negative-binomial log-link function to account for overdispersion typical of count data. These models will incorporate a random effect for each study cluster to adjust for intra-cluster correlation. Environmental covariates for factors, that were not controlled for with the allocation of clusters to trial arms, will be integrated into the models. These are average altitude and the distance from the nearest freshwater source per household, calculated from the mean spatial coordinate of each cluster. Comparative analyses will assess variations in mosquito species proportions across treatment arms to gauge effects of the intervention. Mosquito sporozoite rate will be reported as the proportion of mosquitoes (%) with sporozoites present per sample. The outcomes will be compared across treatment using the same linear regressions models employed for mosquito species composition. The prevalence of resistance to pyrethroids in *Anopheles* mosquitoes will be reported as the proportion of samples that are susceptible (98–100% resistance), possibly resistant (90–97% resistance) or confirmed resistant (less than 90% resistance) per sample. The outcomes will be compared across treatment arms. To address potential confounding factors and account for non-independence of data within clusters, logistic regression models will be employed, as described for the primary endpoint.

Household survey and acceptability survey data will be summarised using basic descriptive statistics. Mixed methods will be applied for the quantitative and qualitative data that have been obtained from the entire study. Data will be entered into Excel (Microsoft) and thereafter exported into a software for analysing qualitative data, such as NVivo (Lumivero) or MAXQDA (VERBI GmbH). We will employ thematic analysis on qualitative data to group sentiments and concepts as patterns collected in the data. These findings will be reported as synthesised narratives that illustrate the most primary perceptions, experiences and acceptability of the intervention, as well as to provide additional context through description of quantitative data when appropriate.

Quantification of the temporal changes in concentration of transfluthrin present in the air will be calculated as nanograms per litre of air sampled and compared for the sampling time points. The results will be presented using summary statistics, in a graphical format and the outcomes will be compared across treatment arms. To address potential confounding factors and account for non-independence of data within clusters, logistic regression models will be employed, as described for the primary endpoint.

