### Outcomes {12}

The primary outcome measured in this study will be the average reduction in malaria infection prevalence in children ≤ 5 years of age from baseline to month 12, as measured by RDT and microscopy. Secondary outcome measures include:
CDC light trap indoor density for anophelines and by anopheline species, as measured by light trap collections from 7 pm to 7 am on a 6 monthly basis. Change in mosquito density at baseline and month 12 between arms will be analysed by negative binomial regression with a random effect for study cluster.Anopheline-human contact (indoor and outdoor) using human biting rate (HBR) as an indicator for all anophelines and by anopheline species, as measured by HLC during 6-h intervals on a 6-monthly basis. Change in HBR at baseline and month 12 between arms will be analysed by negative binomial regression with a random effect for study cluster.Anopheline infectivity using sporozoite rate as an indicator for all anopheline and by anopheline species, as measured by laboratory detection of sporozoites in mosquito heads and thoraces from a subsample of anophelines collected during CDC light trap and HLC collections.Insecticide resistance, as measured by WHO tube test bioassay, during the intervention phase. Confirmed resistance, possible resistance and susceptibility will be calculated through evaluating knockdown and mortality rates.Subject behaviour and household features related to exposure to malaria and use of existing control tools, as measured by quantitative and qualitative surveys on a 6-monthly basis. Survey outputs will be summarised using basic statistics.Concentration of transfluthrin in air over the duration of an evening’s use or the Mossie-GO™ and the impact of indoor temperature on the concentration, as measured by air sampling at months 9 and 12. Mean concentration will be compared between arms.Acceptability of Mossie-GO™ in these communities, as measured be quantitative and qualitative surveys at 6 and 12 months and FGDs at 12 months. Outputs will be summarised using basic statistics and thematic analysis.Safety of intervention through monitoring of AEs and SAEs. Measured actively and passively throughout the duration of the study and total number of events and type of events will be compared between study arms.

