##### Entomological monitoring

Within each of the 56 clusters, CDC light trap collections will be conducted in 7 households from 7 pm–7 am at baseline, 6 and 12 months to allow assessment of the impact of intervention on the density of *Anopheles* mosquitoes indoors. Data collectors will be trained in setting up and taking down CDC light traps and heads of households may be trained to switch on/off the traps at the required time when necessary. Households will be selected at random for CDC light trapping at each timepoint. Additionally, HLCs will be performed indoors and outdoors for 3 consecutive nights in 3 households within each of 10 clusters (30 households total) at baseline, 6 and 12 months to determine the effect of the intervention on the host seeking behaviour of mosquitoes. Alongside the data collector, the head of household and community members will be trained to conduct the HLC and will be supervised during data collection. The clusters and households selected for HLCs will be selected at random for each time point.

Caught mosquitoes from CDC light trapping and HLCs will be examined to record vector species diversity, density and sporozoite rates at each time point. To characterize the insecticide resistance profile of the vector population in the study area, a series of WHO tube tests will be conducted in both districts (Jinja and Buikwe). Larval dipping will be conducted at selected sites, with larvae reared to adults in laboratory facilities and tested for insecticide resistance following WHO protocols and using standard WHO data collection forms [24].

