## Statistical methods

### Statistical methods for primary and secondary outcomes {20a}

#### Statistical analysis of the primary endpoint

The primary outcome will be reported as the proportion of children ≤ 5 years of age infected with malaria (%) at the cluster level. The proportion of children with malaria infection will be summarised at the cluster level and the intervention level. The outcomes will be compared across treatment arms. To address potential confounding factors and account for non-independence of data within clusters, logistic regression models will be employed. These models will incorporate a random effect for each study cluster to adjust for intra-cluster correlation.

Both unadjusted and adjusted models will be presented. The primary model will be as outlined above, and an adjusted model will include additional factors to account for variation at baseline and features that are highly predictive of the primary endpoint. These will include the following: Environmental factors known to have a strong influence on malaria incidence, including the average altitude, calculated from the mean spatial coordinate for each cluster, and the average distance from the nearest freshwater body, calculated from the mean spatial coordinate for each cluster; Use of other vector control interventions; Socio-economic status of the household; Architectural features of the household, or modification made to the household, that are related to mosquito entry; and Season of data collection.

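### The insecticide-resistance cut-offs are written on percent resistance instead of percent mortality, which inverts the classes, and the planned arm comparison is not matched by the sampling described

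*Protocol article*

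**What the plan says.** **Classification.** The protocol article, under Statistical analysis of the secondary endpoints, defines three classes: "susceptible (98–100% resistance), possibly resistant (90–97% resistance) or confirmed resistant (less than 90% resistance"). Under Outcomes {12}, the same classes have a different basis: "Confirmed resistance, possible resistance and susceptibility will be calculated through evaluating knockdown and mortality rates".

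**Comparison.** Directly after the cut-offs, the analysis section adds for this outcome: "The outcomes will be compared across treatment arms". The method is that "logistic regression models will be employed, as described for the primary endpoint". The primary-endpoint section says of that model: "These models will incorporate a random effect for each study cluster to adjust for intra-cluster correlation".

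**Sampling.** Under Entomological monitoring, the purpose is given as "To characterize the insecticide resistance profile of the vector population in the study area". For this, "a series of WHO tube tests will be conducted in both districts (Jinja and Buikwe"), and "Larval dipping will be conducted at selected sites". The participant timeline marks resistance sampling once, at month 12.

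**Objective.** Under Objectives {7}, the resistance objective is to measure prevalence. It does not mention the arms. The first secondary objective, on species composition, density and sporozoite rate, explicitly compares them.

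**The concern.** There are two separate problems.

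First, the label and the quantity run in opposite directions. A class called susceptible should hold samples with little resistance, yet it is assigned to the highest resistance percentages. Coded as written, the rule would misreport the resistance status of the local vectors. That matters for interpretation: the Introduction gives insecticide resistance as a reason for new tools and argues that transfluthrin products may work where pyrethroid resistance is present.

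Second, the analysis asks for a contrast between randomised arms with a cluster term, while the sampling described is organised by district and site. If sites cannot be assigned to clusters, the cluster random effect has nothing to attach to. A difference between arms could then be read as an effect of the device without support from the randomisation.

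**Working it through.** No sample size, power or error rate is stated for this outcome, so the check is logical, with simple complement arithmetic.

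**Step 1: the classification.** Inputs are the three cut-offs (Statistical analysis of the secondary endpoints) and the measured quantity, mortality (Outcomes {12}). Assumption: survivors count as resistant, so percent resistant = 100 − percent mortality.

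| Mortality | Percent resistant | Label as printed | Label with the same cut-offs on mortality |
|---|---|---|---|
| 100% | 100 − 100 = 0% | confirmed resistant | susceptible |
| 99% | 100 − 99 = 1% | confirmed resistant | susceptible |
| 95% | 100 − 95 = 5% | confirmed resistant | possibly resistant |
| 50% | 100 − 50 = 50% | confirmed resistant | confirmed resistant |
| 5% | 100 − 5 = 95% | possibly resistant | confirmed resistant |
| 1% | 100 − 1 = 99% | susceptible | confirmed resistant |
| 0% | 100 − 0 = 100% | susceptible | confirmed resistant |

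The printed rule gives confirmed resistant whenever resistance is below 90%, that is, mortality above 10%. The mortality reading gives it whenever mortality is below 90%. The two therefore agree only for mortality strictly between 10% and 90%. Outside that range the printed label is wrong, and at the two extremes it is the exact reverse.

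On mortality the bands are coherent: susceptible at 98–100% (0–2% surviving), possibly resistant at 90–97% (3–10% surviving), confirmed resistant below 90% (more than 10% surviving).

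A value between 97% and 98%, such as 97.5%, falls in no band unless percentages are first rounded to whole numbers. This is minor.

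**Step 2: the arm comparison.** The entomological collections set side by side:

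| Collection | Unit stated in the article | Tied to clusters? |
|---|---|---|
| CDC light traps | 7 households in each of 56 clusters | yes |
| Human landing catches | 3 households in each of 10 clusters | yes |
| Tube tests | both districts, larvae from selected sites | not stated |

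The unit of randomisation is the cluster, roughly a village (Sequence generation {16a}). District is a stratification factor, so each district should contain clusters of both arms. Knowing a larval site's district therefore does not tell the analyst its arm; only a link from site to cluster would. No such link is described, and neither the number of sites nor the number of mosquitoes is given. No figure for the arm comparison can be recomputed.

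**The case against.** **On the cut-offs.** The error is plainly a slip. The Outcomes section names knockdown and mortality, and Entomological monitoring says that testing follows WHO protocols and standard WHO forms. Staff who follow those would not call a sample in which every mosquito survives susceptible. This stands as regards likely harm: a reader might infer that the trial's conclusion on resistance will be reversed, and the documents do not support that. It does not remove the error, because the statistical section is the only place with numerical cut-offs and they contradict both their own labels and the Outcomes section.

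**On the sampling.** A condensed article can leave the list of larval sites to the full protocol or operating procedures. This also stands. A reader might infer that no arm-level sampling exists and that no valid arm contrast is possible. The text does not show that; it shows only that no link to cluster or arm is described. Two supporting arguments for the stronger reading also fail:

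- *No baseline round.* A randomised comparison at month 12 does not need a baseline to be valid. Without one, change over time cannot be assessed, but that is a different question.
- *Both arms in each district.* This does not rule out an arm contrast. If sites were tied to clusters, it would allow a comparison within districts.

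What remains is a mismatch inside the article: an arm comparison with a cluster term on one side, and a descriptive objective with district-level sampling on the other.

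**Conclusion.** The classification is wrong as written. This follows from the text alone, since the cut-offs contradict both their labels and the stated basis in mortality. The size given, wrong labels at mortality of 90% or more and of 10% or less, rests on the assumption that survivors count as resistant. In practice the consequence is likely to be small if the laboratory classifies on mortality.

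The second part holds conditionally. The planned arm comparison does not match the sampling described or the objective, but the article does not establish that cluster-level sampling is absent. Whether the contrast can be interpreted depends on how larval sites map to study clusters.

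Both parts concern one secondary outcome. The primary endpoint and its power are not affected.

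**What to change.** 1. In the section on secondary endpoints, replace *resistance* by *mortality* in all three cut-offs, so that they agree with the Outcomes section. As a minor tidy-up, define the middle band as 90% to below 98%.
2. State whether each larval site belongs to a study cluster.
   - If sites are tied to clusters, say so, and give the number of sites and of mosquitoes tested per cluster and arm. The arm comparison with a cluster random effect can then be kept.
   - If not, report mortality with confidence intervals descriptively by district and insecticide, in line with the objective, and present no arm contrast as an intervention effect.

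The first change costs only wording. The second costs either a short clarification of the sampling or the loss of one secondary comparison. Both should be settled before the classification is coded.

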### Objectives {7}

The study’s primary objective is to demonstrate and quantify the protective efficacy of Mossie-GO™, a transfluthrin-based active spatial repellent device, in reducing prevalence of malaria infection in children ≤ 5 years of age, as determined by rapid diagnostic test (RDT) and microscopy. Secondary objectives are incorporated to measure the impact of the intervention on entomological correlates of transmission, user acceptance of the device and quantification of transfluthrin concentration in the air. Secondary objectives are:
To compare mosquito species composition, population density and sporozoite rates in mosquitoes caught using indoor CDC-light traps and Human Landing Catches (HLC) between intervention and control arms.To measure the prevalence of resistance to pyrethroids in *Anopheles* mosquitoes using WHO tube test bioassay.To collect information on subject behaviour related to exposure to malaria and use of existing control tools via household surveys.To quantify temporal changes in concentration of transfluthrin present in the air over an evening and residual concentrations over the duration of the study and measure the correlation between indoor temperature and the concentration of active in the air.To assess the acceptability of Mossie-GO™ in the study population as an indicator of whether this device could be scaled up in similar settings in the future using surveys, interviews and focus group discussions (FGDs).To assess the safety of intervention through monitoring of adverse events (AEs) and serious adverse events (SAEs).

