### Intervention description {11a}

The Mossie-GO™ repellent device is approximately 75 mm × 51 mm and can be fitted with repellent discs impregnated with transfluthrin and a carrier oil. These discs sit above a fan that is powered by a small motor charged by solar energy. The device, containing treated discs, is expected to both prevent bites and cause some mortality to mosquitoes when switched on for 8–12 h overnight. The trial design includes a placebo product of matched design to the Mossie-GO™ device but with discs containing no active ingredient or carrier oil.

At baseline (month 0) both the intervention and control arms will receive the Mossie-GO™ and a disc to last 1 month. Discs will be replaced on a monthly basis and old discs will be discarded by the study team.

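### The air-concentration endpoint, measured in nanograms per litre, is assigned logistic regression, which does not fit a continuous outcome; separately, the sporozoite sentence calls its model linear while pointing to models that are logistic.

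*Protocol article*

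**What the plan says.** **Air concentration.** Under Statistical analysis of the secondary endpoints, transfluthrin in air "will be calculated as nanograms per litre of air sampled and compared for the sampling time points". Summary statistics, graphs and a comparison across arms are to follow. The paragraph then closes with the model: "logistic regression models will be employed, as described for the primary endpoint". The same wording occurs twice earlier in that section, for species composition and for insecticide resistance. The occurrence at issue is the last one, on air concentration.

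Two other sections bear on this endpoint. Outcomes {12} states: "Mean concentration will be compared between arms". Objectives {7} includes the aim to "measure the correlation between indoor temperature and the concentration of active in the air".

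**The model referred to.** Under Statistical analysis of the primary endpoint, the response is infection status, summarised in these terms: "The primary outcome will be reported as the proportion of children ≤ 5 years of age infected with malaria (%) at the cluster level". The analysis is logistic regression with a random effect for cluster.

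**Sporozoite rate.** The endpoint is a proportion: "Mosquito sporozoite rate will be reported as the proportion of mosquitoes (%) with sporozoites present per sample". Its model is given as follows: "The outcomes will be compared across treatment using the same linear regressions models employed for mosquito species composition". Earlier in the same section, species composition is assigned logistic regression.

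**The concern.** A model written for a yes/no response has been attached to a measured concentration. It looks like a sentence carried over from outcomes that are proportions to one that is not.

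Air sampling is meant to help interpret the entomological and epidemiological results (Trial design {8}), so it is the trial's evidence on exposure. If the named model cannot be used, the analyst has to choose another one outside the plan. That choice could come after the air results are seen, and those results largely reveal arm. The temperature objective would also have no usable method in the text.

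For sporozoites, one sentence describes its model in two incompatible ways, so a reader cannot tell which model will be run.

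**Working it through.** The document gives no figure to reproduce here. The check compares each outcome's scale with the model assigned to it.

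**Air concentration**

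1. Scale: nanograms per litre, so continuous and non-negative (Statistical analysis of the secondary endpoints).
2. Model: logistic regression with a cluster random effect, as for infection status. It needs a response of 0 or 1 per observation, or a count of successes out of a known number of trials. A concentration is neither.
3. Bridge between the two: none. No cut-off, detection limit or detected/not-detected version of the outcome is defined.
4. Illustrative fit on assumed data (28 households, taken as 14 per arm; placebo set to zero; active values lognormal): the software rejects the raw concentrations because the response lies outside 0 to 1. Even if every value happened to fall below 1, the fit would have no meaning, because it would change with the unit: 1 ng per litre is 1,000 ng per cubic metre.
5. Against Outcomes {12}: that section targets a difference in means. Logistic regression estimates an odds ratio for an event.
6. Against Objectives {7}: a correlation with temperature needs the concentration on its own scale. Temperature is not mentioned in the air-analysis paragraph, nor is it among the adjustment factors listed for the primary endpoint.

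**Amount of data for a replacement model**

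- Households: 2 in each of 14 clusters, 2 × 14 = 28.
- Measurements, if each household is sampled at both intervals in both months: 28 × 2 × 2 = 112.
- Active arm, if the 14 clusters split equally (not stated): 7 clusters, 7 × 2 = 14 households per month, 14 × 2 × 2 = 56 measurements.
- Households are drawn anew at each time point, so a household effect would rest mainly on the two intervals within one evening.

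**Sporozoite rate**

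| Element | What the text gives |
|---|---|
| Outcome | Proportion of mosquitoes positive, so binary per mosquito |
| Model by name | Linear |
| Model by reference | That of species composition, which is logistic with a cluster random effect |

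The name and the reference disagree. Outcomes {12} names no model for this endpoint, so it does not settle the matter.

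**The case against.** **This is detail for the statistical analysis plan.** A plan that is not shown may well hold a suitable model. But the article does not leave the model open; it names one that does not suit the outcome and that conflicts with its own Outcomes section. The objection does not remove the point.

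**Time and arm are covered elsewhere.** A reader might infer that the whole air objective goes unanswered. The document does not support that. It promises a comparison across sampling time points with summary statistics and graphs, and Outcomes {12} gives the arm comparison a clear target. What stands is narrower: the regression sentence conflicts with that target, and no usable method is named for temperature.

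**Dichotomising.** A reader might infer that the analysis fails through complete separation, since the placebo has "discs containing no active ingredient or carrier oil". In the assumed data above, the detected/not-detected fit did fail for that reason. But the document never proposes to dichotomise. Separation would also require every placebo sample to be a non-detect and every active sample a detect. No detection limit is given, and the article notes that transfluthrin is used in many consumer products, so background detections are possible. The fault as written is a mismatch of model and scale.

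**Sporozoites.** A reader might infer that ordinary linear regression has been chosen and that its standard errors and limits will be invalid. That follows only if the word linear overrides the reference to the species-composition models. It is more probably a slip, or shorthand for generalised linear. Taken literally, and with inputs that are not in the document, the fit would be poor:
- With 10 mosquitoes per sample, the share of samples at exactly 0% is 0.99^10 = 0.90 at a 1% rate and 0.95^10 = 0.60 at 5%.
- With 200 mosquitoes at 1%, p ± 1.96 × √(p(1 − p)/n) = 0.01 ± 1.96 × √(0.01 × 0.99/200), or −0.4% to 2.4%. At 2% the same formula gives 0.06% to 3.9%, which stays above zero.

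These figures show why the wording should be settled. They do not show an error that the trial will make.

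**Conclusion.** The air-concentration point stands. A binary-outcome model is assigned to a continuous outcome with no threshold defined. It contradicts the comparison of means in Outcomes {12} and cannot give the temperature correlation in Objectives {7}. This conclusion needs no assumed inputs.

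The sporozoite point stands only as an internal contradiction to be reconciled, not as a settled choice of an unsuitable method.

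No sample size, power or error rate changes. Only secondary endpoints are affected, and the primary analysis is untouched. It should be corrected because it is wrong as written and cheap to put right.

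**What to change.** **Air concentration.** Replace the logistic sentence in the air paragraph with a model for a continuous, skewed, clustered outcome. One option:
- Keep the between-arm comparison of mean concentration from Outcomes {12}, allowing for clustering.
- Fit the time and temperature terms in the active arm, because placebo discs hold no active ingredient and placebo values are expected to be near zero. Use a linear mixed model on log concentration with terms for sampling interval, month and indoor temperature, and a random effect for cluster. Add a household effect only if it can be estimated with 28 households.
- State the rule for values below the detection limit.

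A simpler log-scale analysis would also serve if the mixed model proves too much for the data.

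**Sporozoite rate.** Change linear to logistic (binomial) mixed regression with a cluster random effect, so that the name matches the models referred to.

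**Cost.** Minor rewording and slightly more analysis work, with no change to sampling or data collection. The wording should be settled before the air results are examined.
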